### Secondary outcome measures

Secondary outcome measures will be administered at baseline and follow-up assessments to inform about possible effectiveness and preparation for a future definitive trial of PM+EP. The Hopkins Symptom Checklist-25 (HSCL-25) is a 25-item validated psychometric scale assessing symptoms of depression (15 items) and anxiety (10 items).^35^ Two of the depression items specifically relate to associated somatic symptoms. The items are rated on a 4-point Likert scale (range=25–100), ranging from 1 (not at all) to 4 (extremely).

PTSD symptom severity and diagnosis will be established with the PTSD Checklist for DSM-5 (PCL-5).^36^ The PCL-5 is a 20-item checklist, corresponding to the 20 symptoms of PTSD as described in the Diagnostic and Statistical Manual of Mental Disorders, Fifth Edition (DSM-5). Each item is scored on a 5-point scale, ranging from 0 (not at all) to 4 (extremely). When the symptom severity score is rated as two (moderate/threshold) or higher, a symptom is considered present. Total symptom severity is calculated by summing the scores of the 20 items (range: 0–80), with higher scores indicating worsened severity of post-traumatic stress symptoms.

The Psychological Outcomes Profiles (PSYCHLOPS) will be used to indicate the client’s perspective of change in their psychological distress level after therapy.^37^ PSYCHLOPS has four questions measuring three domains; the problem(s) bothering the individual (two questions), and how these problems affect the daily functioning and well-being. Scores range from 0 to 5 and higher scores represent more psychological difficulty (range=0–20).

Social support will be measured through a 1-item question assessing ‘bonding social capital’ from the Stockholm Public Health Cohort.^38^ Participants will be asked: ‘Do you know any people who can provide you with personal support for personal problems or crises in your life?’. The response will be categorised as either high social support or low social support.

The Client Service Receipt Inventory (CSRI)^39^ will be used to track the healthcare service use and medications that the participant has received in the 3 months preceding their entry to the study and over the course of the study.

The WHO 5-item well-being Index (WHO-5) will be used to measure subjective general well-being. The questionnaire is a 5-item scale assessing general psychological well-being and quality of life as opposed to well-being tied to a certain psychopathology.^40^ Items are scored on a 6-point scale ranging from 0 (at no time) to 5 (all of the time); total scores are the sum of the individual items ranging from 0 to 25, with higher scores corresponding to increased well-being.

Lastly, the Agency-Subscale State Hope Scale (Adult version; SHS-A) will be used to measure hope among study participants.^41^ The agency subscale of the SHS is a three-item scale measuring goal-directed behaviour during the intervention. Items are scored on an 8-point Likert scale ranging from 1 (definitely false) to 8 (definitely true). Total scores for agency are calculated by summing the item-level scores (range: 3–24), with higher scores indicating more goal-directed behaviours.

### Other measures

Exposure to traumatic events will be assessed through a Traumatic Events Checklist. The checklist contains 29 forms of traumatic events that the participants may have experienced during their displacement and subsequent travel to Sweden. The checklist was developed and used among refugee populations residing in several contexts^20 23 24 42^ and further adapted to the Swedish context prior to use.

The Post-Migration Living Difficulties Checklist (PMLD)^43^ will be used to measure the level of postmigration challenges experienced by the participant during the last 12 months. The checklist contains 17 items measured on a 5-point scale ranging from 0 (not a problem) to 4 (a very serious problem). Items that are either scored 3 or 4 are considered positive responses indicating a living difficulty. A total count of living difficulties is computed by summing the number of items, scoring either 3 or 4. For this study, two new items will be added to the list: (1) being bullied or rejected by peers and (2) arguments with parents over new friends and/or hobbies. Additional adaptations include adapting the item difficulties with employment, difficulties with education/employment and conflicts with social workers/other authorities to include teachers.

### Assessor competence

Data will be collected remotely through telephone assessments. The assessors undergo a 2-day training on questionnaire administration, basic interviewing skills, common mental health disorders, psychological first aid and ethics of research. In addition to this, assessors will have the opportunity to receive supervision on needs for referral from clinical staff and on the assessments by the trainer. Assessors will be available for all languages included in the study. All assessors should be fluent in either Swedish or English. They will be blinded to the allocation of the participants; during follow-up assessments and subsequent to the intervention period, assessors will instruct participants not to reveal the intervention that they received. The assessors will be recruited by Save the Children Sweden.

### Study procedure

Potential participants will be recruited through ongoing Save the Children Sweden activities in three regions of Sweden (East, South and West). Save the Children Sweden has available programmes for children, young people and caregivers nationally. In 2024, activities reached almost 40 000 children and young people. These programmes included psychosocial activities, group-based mental health support and safe meeting places where displaced persons were able to receive support. Recruiting staff at Save the Children will inform all young people about who may meet the eligibility criteria about the possibility of participating during their regular activities. If recruitment for the final sample size is not possible through ongoing Save the Children services, advertisements will be placed on social media with information about the study. Potential participants who indicate interest in participation are then referred to the study team and perform an initial screening assessment of eligibility using the WHODAS 2.0, K10 and a structured suicide risk evaluation assessment. Participants will be invited to the baseline assessment if they meet the eligibility criteria stated above and consent to participating in the trial. At baseline, participants will complete the following assessments: HSCL-25, PCL-5, PSYCHLOPS, WHO-5, bonding social capital, SHS-A and CSRI. In addition, participants will be asked to complete PMLD and the traumatic event checklists. Following the assessment, participants will be randomly assigned in a consecutive manner, using a 1:1:1 ratio for the randomisation process. The randomisation sequence will be computed by an independent researcher from KI using computerised software and allocation will be conducted by Save the Children Sweden; allocation is concealed from all study staff. Following the completion of the intervention, participants will be invited to complete 1-week postintervention (7-week) and 3-month follow-up (18-week) assessments.

After the 3-month follow-up, participants will be invited to take part in the qualitative process evaluation. Individual semistructured qualitative interviews will be conducted by researchers and psychologists. Interviews with participants and their families will be held in their preferred language. For key informants, interviews will be conducted on an ongoing basis throughout the trial, and for PM+EP/PM+helpers, at the conclusion of their final sessions.

On the completion of the trial, participants identified as requiring more support will receive information and assistance in locating suitable and appropriate follow-up care. For those who were randomised into CAU, PM+ will be offered after the 3 months post-assessment.

### Sample size

Since this is a pilot feasibility trial, no formal power calculations have been carried out. A total number of 60 forcibly displaced youth (20 in each arm) will be included in the study, allowing us to evaluate the feasibility and acceptability of the intervention in the proposed setting, as well as drop-out rates for a future definitive trial. This sample size was determined to be sufficient based on prior similar studies.^44 45^

### Analysis plan

The primary analyses for the feasibility RCT are planned to understand the safety and acceptability of the intervention and to preliminarily understand the within-group changes prior to and following the PM+(EP) Interventions. To accomplish this, both quantitative and qualitative methods will be used. The data will be analysed for the primary outcome and the other continuous measures using repeated measures analysis of variance. Kruskal-Wallis tests will be used if the normal distribution assumption fails. For the feasibility evaluation, intervention-specific analysis (fidelity, attendance to sessions) will be carried out. The qualitative process evaluation data will be analysed following thematic analysis through NVivo Scientific Software. To estimate potential effectiveness for a future trial, intention-to-treat analyses will be employed. Cohen’s d, based on pooled SD, will be used to calculate the treatment effect size of the PM+EP (based on primary outcome).

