One of the earliest developed scalable psychological interventions was problem management plus (PM+),^17^ which aimed to allow for mental health services to be delivered in places with limited mental health resources. PM+specifically targets people experiencing moderate levels of psychological distress and aims to relieve symptoms related to common mental disorders. The intervention is composed of evidence-based strategies related to problem-solving and behavioural activation and consists of four core components: (1) managing stress, (2) managing problems, (3) get going, keep doing, and (4) strengthening social support.^17^ Several studies have demonstrated the effectiveness of PM+ in adults residing in low-income and middle-income countries through individual ^18 19^ and group formats.^20^,^22^ More recently, the feasibility and effectiveness of the intervention in HICs among refugees have been explored in the Netherlands^23^ and Switzerland.^24^ Although no active ingredients targeting post-traumatic stress symptoms are included in the intervention, PM+ has been shown to reduce individual symptoms of PTSD.^25^ The emotional processing (EP) Theory proposes that effective psychosocial interventions to treat PTSD should include direct modification of the fear structure, which may give rise to symptoms of the disorder, by activating the fear structure using exposure and by integrating more realistic, non-threatening information into it.^26^ Further, recent evidence indicates that processing positive memories and imagining positive events in the future can positively affect mental health outcome.^27^ Given the pervasiveness of experienced traumatic events and PTSD in refugee populations, including in children and adolescents,^5^ it would be worthwhile exploring further whether exposure to memories of negative past events adds to the efficacy of a scalable intervention such as PM+ in reducing symptoms of PTSD and depression, and additionally as to whether it would be feasible to deliver active ingredients of exposure therapy using scalable psychological interventions. To further elucidate the contribution of the retrieval of negative memories in reducing PTSD symptoms, this study seeks to preliminarily compare PM+ with PM+ including an EP component (PM+EP).^28^ The primary aim of this feasibility randomised controlled trial (RCT) study is to evaluate the feasibility and acceptability of the PM+EP and PM+ interventions for forcibly displaced youth residing in Sweden. A secondary aim of this work is to preliminarily compare PM+ with an EP component with PM+ and care of usual.

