### Trial design

The study consists of two phases: a feasibility RCT and a qualitative process evaluation. The feasibility RCT uses a three-armed single-blind randomised controlled parallel group design, comparing PM+, PM+EP and care as usual (CAU) for forcibly displaced persons living in Sweden. We aim to recruit 60 participants who screen positive for moderate psychological distress. Assessments will be conducted at baseline, 1 week after treatment completion (7 weeks) and 3 months after treatment completion (19 weeks). The flow chart of the trial is shown in figure 1. As part of the qualitative process evaluation, we will be exploring beneficiaries’ and implementers’ experiences with the intervention, and practitioners’ and policymakers’ thoughts on the use of PM+/PM+EP more widely in Sweden.

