### Inclusion criteria

Participants will be eligible for the trial if they meet the following criteria:

Forcibly displaced youth aged 16–25 years old who arrived in Sweden after 2015.Elevated levels of psychological distress as determined through the Kessler-10 Psychological Distress Scale (K10; K10 >15).^29^Reduced levels of psychosocial functioning as measured by the WHO Disability Assessment Schedule (WHODAS 2.0>16).^30^Fluent in Swedish or in any language for which validated translations of the study manual and assessment tools were available.

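### The effectiveness target is stated only as within-group change, and Cohen's d for PM+EP has no comparator, time point or usable scale, so the analysis plan does not fix the between-arm comparison that is a secondary aim

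*Protocol article*

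**What the plan says.** The Introduction puts feasibility first: the primary aim is to "evaluate the feasibility and acceptability of the PM+EP and PM+ interventions for forcibly displaced youth residing in Sweden". It then adds: "A secondary aim of this work is to preliminarily compare PM+ with an EP component with PM+ and care of usual". The Trial design section describes a "three-armed single-blind randomised controlled parallel group design, comparing PM+, PM+EP and care as usual (CAU"), and Study procedure allocates "using a 1:1:1 ratio for the randomisation process". Under Sample size, "A total number of 60 forcibly displaced youth (20 in each arm) will be included in the study".

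The section on Problem management plus gives the PM+ arm an extra supportive-counselling session so that its contact time matches that of the EP module.

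The Analysis plan says that the primary analyses concern safety and acceptability and are also meant "to preliminarily understand the within-group changes prior to and following the PM+(EP) Interventions". It names repeated measures ANOVA, with Kruskal-Wallis tests if normality fails, and intention-to-treat analyses for potential effectiveness in a future trial. It ends: "Cohen’s d, based on pooled SD, will be used to calculate the treatment effect size of the PM+EP", based on the primary outcome. Under Feasibility measures, that primary outcome is feasibility and acceptability.

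**The concern.** Within-group change answers a different question from the secondary aim. It does not involve the CAU arm, and it cannot show whether the EP module adds anything to PM+, which is the purpose of the time-matched PM+ arm.

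The effect size does not close the gap. As written it could be PM+EP against CAU, PM+EP against PM+, or post against pre within PM+EP, at either of two follow-ups and on no identified scale.

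The choice matters because participants are selected for high scores: "Elevated levels of psychological distress as determined through the Kessler-10 Psychological Distress Scale (K10; K10 >15"), together with a WHODAS 2.0 score above 16. They are also recruited from ongoing psychosocial programming. Some improvement in every arm, unrelated to PM+EP, is therefore plausible. A within-arm d includes that improvement, while a difference between randomised arms removes it on average. The figure is meant to indicate potential effectiveness for a later trial, so an inflated value would mislead its planning.

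**Working it through.** **Plan's own figure.** 3 arms × 20 = 60, as stated. No power-based figure exists to reproduce: the protocol says that no formal power calculation was done and gives no SD or correlation. Everything below on size therefore rests on assumptions.

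**1. Sections side by side.**
- Introduction, Trial design and the time-matched PM+ arm: comparison between arms.
- Analysis plan, stated target: change within the PM+(EP) arms. No between-arm contrast, group-by-time term or role for CAU is stated.
- Analysis plan, d: pooled SD, no comparator, no time point, tied to an outcome that is not a symptom score.

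**2. Shared improvement, zero treatment effect.** Assumptions: 20 per arm, SD 1, pre-post correlation 0.6, the same improvement δ in all arms, 20,000 simulated trials.
- Within-arm d = mean change in one arm / SD pooled over pre and post.
- Between-arm d = difference in follow-up means / SD pooled over the two arms.

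| δ (SD) | mean within-arm d | pre-post test significant | mean between-arm d | between-arm test significant |
|---|---|---|---|---|
| 0 | 0.00 | 5% | 0.00 | 5% |
| 0.2 | 0.21 | 16% | 0.00 | 5% |
| 0.3 | 0.31 | 30% | 0.00 | 5% |
| 0.5 | 0.51 | 66% | 0.00 | 5% |

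Hand check at δ = 0.3: the SD of change is √(2(1 − 0.6)) = 0.894, so the non-centrality is 0.3/0.894 × √20 = 1.50, in line with about 30%. If the correlation is varied from 0.5 to 0.7, the share of significant trials is 25–38% at δ = 0.3 and 57–78% at δ = 0.5.

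**3. Regression to the mean alone.** Assume that the screening score correlates r1 = 0.7 with the outcome at baseline and r2 = 0.4 to 0.6 at follow-up, and that a share s of those screened passes. With cut-off c, λ = φ(c)/s and k = λ(λ − c):

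d = (r1 − r2)λ / √[((1 − r1²k) + (1 − r2²k))/2]

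Example with s = 0.5 and r2 = 0.5: λ = 0.798 and k = 0.637, so d = 0.2 × 0.798 / √[(0.688 + 0.841)/2] = 0.18.

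| share passing | d, r2 from 0.6 to 0.4 |
|---|---|
| 80% | 0.04–0.11 |
| 50% | 0.09–0.27 |
| 25% | 0.15–0.44 |

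**4. Planning illustration.** At 80% power and two-sided 5%, a true d of 0.3 needs 176 per arm. Adding 0.2 of untreated change makes it look like 0.5, which needs 64 per arm.

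**5. Precision of a between-arm d.** For d near 0, SE = √(2/20) = 0.316 and the 95% half-width is 1.96 × 0.316 = 0.62. With 17 per arm (85% of 20) it is 1.96 × √(2/17) = 0.67. With baseline adjustment at 20 per arm it is 1.96 × √(0.1(1 − r²)), which is 0.54 at r = 0.5 and 0.44 at r = 0.7.

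**The case against.** The strongest reply is that the Analysis plan already points to a between-group analysis. Kruskal-Wallis compares independent groups and is not a test of change within one arm. A pooled SD is the usual denominator of a two-group d. Intention to treat normally goes with analysis by randomised arm, and a repeated measures ANOVA can carry arm and group-by-time terms. The within-group wording sits in the sentence on the primary analyses, while the effect size comes later. An analysis plan not shown may also define the contrasts.

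Much of this stands, and it limits the point. A reader might infer that d is a pre-post figure and that natural recovery will be reported as treatment effect. The protocol does not say so: no sentence defines d as pre-post or equates within-arm change with the effect. A reader might also infer that the three-way comparison is the main aim and that 20 per arm was chosen to support it. In fact the comparison is secondary and preliminary, and the Sample size section justifies 60 by feasibility, acceptability and drop-out.

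The possible bias may also be modest. Selection is on K10 and WHODAS, whereas the symptom outcomes are other scales first taken at a later baseline. Nor does the protocol say that the next trial will be sized from this d.

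What does not stand is that the hints settle the matter. Kruskal-Wallis is only a fallback and does not test the change that the plan names. A pooled SD can pool pre and post, intention to treat fixes the analysis set rather than the contrast, and no group-by-time term is stated. Nor is this merely detail left to another document: the article affirmatively states a target that does not serve its own comparative aim.

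**Conclusion.** The point holds as an inconsistency between a stated secondary aim and the stated quantitative target, together with an effect size that lacks a comparator, a time point and a usable scale. The bias is conditional: present if d is computed within the arm, absent on average if it is computed between randomised arms. The text does not settle which.

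If the within-group target is followed, an assumed shared improvement of 0.3 SD gives a d of about 0.3 from a treatment with no effect. Regression to the mean alone gives about 0.04 to 0.27 if 50–80% of those screened pass. These sizes rest wholly on assumed correlations, selection shares and drift.

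This should be fixed but is not critical, because the primary feasibility criteria do not depend on it.

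**What to change.** In the Analysis plan, make the effectiveness target the between-arm differences PM+EP versus PM+ and PM+EP versus CAU. Name a symptom scale (for example HSCL-25 or PCL-5) and a follow-up (7 weeks or 3 months), adjust for the baseline value already collected, and report 95% CIs. Define Cohen's d as each of these differences divided by the pooled SD, one d per named comparator, and drop its link to the primary outcome. State that within-arm change is descriptive and is not an effect size for a later trial.

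This changes wording only and needs no new data. The price is a less favourable and visibly imprecise d: about ±0.62 unadjusted with 20 per arm, or ±0.44 to ±0.54 with baseline adjustment at the assumed correlations of 0.7 to 0.5. The wording should be settled before anyone sees outcome data by arm, so that the comparator and scale are not chosen afterwards.

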### Feasibility measures

The primary outcome of this study will be the feasibility and acceptability of the delivery of PM+EP in refugee youth. Feasibility will be determined through criteria related to consent and recruitment rates (>70%), attendance to PM+/PM+EP sessions (>70%), protocol adherence by helpers (>75%) and the number of AEs (<10%). In this study, AEs were defined as any unwanted experiences during the study, regardless of relation to PM+or PM+EP. Serious AEs (SAEs) are events causing death, life threat, hospitalisation or its prolongation, permanent disability or other significant medication conditions not necessarily connected to the intervention. All AEs/SAEs will be reported and followed, with specialist referral as needed. Regarding the feasibility of the research procedure, the completion of the baseline and follow-up assessments will be assessed (>85%). In addition, the qualitative process evaluation will further elucidate information of the acceptability of the interventions.

Protocol adherence will be determined through two methods. The first is a self-rated fidelity checklist that the PM+/PM+EP facilitators will fill out at the end of each session. This will contain each of the elements from the completed session, and facilitators will be asked to identify what items they completed and which items they may have missed to assess the degree of fidelity to the manualised intervention. second, audio recordings of sessions will be taken if participants provide informed consent for recording. A random sample of 10% of recordings will be scored independently by two research assistants.

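### Repeated measures ANOVA in its standard form drops anyone who misses a visit, so it does not by itself deliver the promised intention-to-treat estimate

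*Protocol article*

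**What the plan says.** All references are to the protocol article.

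- **Method (Analysis plan):** "The data will be analysed for the primary outcome and the other continuous measures using repeated measures analysis of variance". The one stated alternative is triggered by the shape of the distribution, not by missing visits: "Kruskal-Wallis tests will be used if the normal distribution assumption fails".
- **Principle (Analysis plan):** "To estimate potential effectiveness for a future trial, intention-to-treat analyses will be employed".
- **Effect size (Analysis plan):** Cohen's d, "based on pooled SD, will be used to calculate the treatment effect size of the PM+EP (based on primary outcome"). The sentence does not say which participants enter d.
- **Visits (Trial design):** "Assessments will be conducted at baseline, 1 week after treatment completion (7 weeks) and 3 months after treatment completion (19 weeks"). Table 1 labels these T1, T2 and T3 and schedules the symptom scales at all three.
- **Expected completeness (Feasibility measures):** "the completion of the baseline and follow-up assessments will be assessed (>85"%). The Sample size section adds that the trial is meant to inform drop-out rates for a later definitive trial.
- **Size and allocation:** "A total number of 60 forcibly displaced youth (20 in each arm) will be included in the study" (Sample size), "using a 1:1:1 ratio for the randomisation process" (Study procedure). Randomisation follows the baseline assessment.

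**The concern.** The classical repeated measures ANOVA works on a complete participant-by-visit table. A participant with T1 and T2 but no T3 is removed entirely, including the T2 score that was collected; the same happens to one with T1 and T3 but no T2. What remains is an analysis by allocated arm among people who attended every assessment. That is narrower than an analysis of all randomised participants, which the intention-to-treat sentence leads the reader to expect.

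The article itself anticipates incomplete follow-up, so the situation is likely to arise. Two things are at stake. The first is precision, because the arms have only 20 people. The second is possible bias if missing a visit is related to how the participant is doing and the relation differs between arms. That is conceivable here: PM+EP participants return to a difficult memory over three sessions and CAU participants do not. The estimates affected are those the Secondary outcome measures section collects to judge possible effectiveness and prepare a definitive trial.

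**Working it through.** **Inputs from the protocol article:** three visits (Trial design); 60 participants, 20 per arm (Sample size); completion criterion above 85% (Feasibility measures).

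**Assumptions:** the 85% applies to each follow-up visit; every randomised participant has a baseline, since randomisation follows it; missingness at T2 and T3 is either fully overlapping or independent.

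**Step 1. The plan's own figure.** 3 arms × 20 = 60, which agrees. There is no power calculation to reproduce.

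**Step 2. Participants left after listwise deletion.** With completion *c* per follow-up visit:

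- same people miss both visits: 60 × *c*
- independent misses: 60 × *c*²

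| *c* | Same people: total (per arm) | Independent: total (per arm) |
|---|---|---|
| 90% | 54 (18) | 48.6 (16.2) |
| 85% | 51 (17) | 43.35 (14.45) |
| 80% | 48 (16) | 38.4 (12.8) |
| 70% | 42 (14) | 29.4 (9.8) |

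At 85%, the loss is 60 − 51 = 9 to 60 − 43.35 ≈ 17 randomised participants, or 15% to 28%. The rows other than 85% are an assumed range.

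**Step 3. Behaviour of the method.** On a constructed data set of 10 people × 3 visits with one score removed, a standard repeated measures ANOVA routine refused to run because the data were unbalanced. A mixed model used all 10 people and 29 of the 30 scores.

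**Step 4. Precision at T2, independent misses at 85%.** People with a T2 score: 20 × 0.85 = 17 per arm. People with both T2 and T3: 14.45 per arm. The variance of the T2 change contrast grows by about 17 / 14.45 = 1.18. A simulation with an assumed between-visit correlation of 0.6 gave 1.19.

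**Step 5. Possible bias, as an example only.** None of these inputs is in the article: true effect −0.50 SD; about 24% missing T3 in PM+EP, more often those with a worse T2 score; 10% missing T3 in the other arms. Overall T3 completion is then (76 + 90 + 90) / 3 = 85.3%. Simulated complete-case results:

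- T2 effect −0.56 to −0.58, so 0.06 to 0.08 SD too favourable to PM+EP
- T3 bias 0 to 0.02 SD

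Against a simulated standard error of 0.334 SD for the complete-case T2 contrast, this is 0.06 / 0.334 = 0.18 to 0.08 / 0.334 = 0.24 of one standard error. If those doing better were the ones to skip T3, the sign would reverse: by symmetry the T2 effect would be about −0.44 to −0.42.

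**The case against.** Several stronger readings are tempting, and the article does not support them.

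- **That the plan states a complete-case analysis.** It does not. No sentence mentions completers or deletion of incomplete records. The exclusion follows from the standard form of the named method.
- **That the two sentences contradict each other.** They do not exclude each other. Intention to treat means first of all analysis in the arm of allocation, and the ANOVA could be run after imputation or replaced by its mixed-model form. The sentences are unconnected rather than incompatible.
- **That Cohen's d inherits the loss.** The article does not tie d to the ANOVA's participants. A d at T2 could use everyone seen at T2, and the bias in Step 5 would then not arise for it.
- **That 14.5 per arm is what the plan tolerates.** This needs a per-visit reading of 85% and independent misses. If 85% means participants completing every assessment, at least 51 of 60 remain, and 72% (0.85 × 0.85) would fail the criterion.
- **That sphericity is a further defect.** A correction for it is routine detail for a statistical analysis plan, and unequal spacing does not invalidate an ANOVA with visit as a category.

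It can also be said that rules for missing data are commonly left to the full protocol or analysis plan, neither of which is shown. That is right, and silence on imputation is not the point. What remains is that the article does fix a method, and that method, as named, needs something added before it yields the estimate promised beside it. A better and standard choice is available.

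**Conclusion.** The point holds in limited form. Repeated measures ANOVA over three visits, applied to unimputed data, would leave out randomised participants who have observed outcomes, so it does not on its own provide the intention-to-treat estimate. On the per-visit reading of the 85% criterion the loss is 3 per arm (same people miss both visits) to about 5.5 per arm (independent misses).

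The direction and size of any bias cannot be known from the article. In the worked example it is under a quarter of a standard error at T2 and close to nil at T3. The consequences are confined to secondary, preliminary estimates in an unpowered feasibility trial. The criteria for recruitment, attendance, adherence, adverse events and assessment completion do not depend on this analysis. Severity is moderate: a worthwhile, inexpensive improvement, not a flaw that threatens the trial's main purpose.

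**What to change.** In the Analysis plan section, replace the repeated measures ANOVA with a linear mixed model fitted by REML:

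- all available scores from all randomised participants, in the arm of allocation
- visit as a category, with arm-by-visit terms
- unstructured within-person covariance
- small-sample degrees of freedom, such as Kenward-Roger

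Report PM+EP minus PM+ and PM+EP minus CAU, with confidence intervals, at T2 and at T3. State that the standardised effect size is based on the same participants. Keep the complete-case ANOVA as a sensitivity analysis.

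**Cost:** a change of wording and standard software, with no new data and no change to visits or sample size. The model relies on outcomes being missing at random given the observed scores and arm. That is weaker than what a complete-case analysis requires, but it cannot be verified and should be stated as an assumption. If the ANOVA is to be kept as the main analysis, the section should at least say how missing visits are filled in, so that it matches the intention-to-treat sentence.
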